### 2.3 Research Flowchart

**Patient Information Sheet sent by Central TOP Booking Service when patients ring for their TOP appointment.**

**Screening and Recruitment at the TOP Provider Unit when patients attend for their TOP consultation + Baseline Data collection with questionnaire at recruitment**

**Randomised to Intervention and Control Arms**

**Intervention**

**Control**

**Research nurse/fellow will contact patients in the intervention arm by telephone during the week following their abortion procedure to arrange appointment for the 2-4 week follow up consultation (telephone/face-face depending on the patients’ preference) with the Specialist in Reproductive and Sexual Health**

**and also inform them about the telephone follow-up at 3 months and 6 months**

**2 – 4 weeks post abortion follow-up consultation for contraceptive support by telephone/face-face clinic visit with Reproductive and Sexual Health Specialist (history, physical examination +/-, STI tests +/-, treatment +/-, contraceptive provision +/-), follow up arrangements as required**

**3 months post abortion telephone interview by Research Nurse/Fellow and contraceptive support and follow up arranged as required**

**6 months post abortion telephone interview by Research Nurse/Fellow with questionnaire to assess contraceptive uptake, compliance and continuation**

**6 months post abortion telephone interview by Research Nurse/Fellow with questionnaire to assess contraceptive uptake, compliance and continuation**

**Data Linkage with Lambeth Public Health data warehouse +/- National Abortion Data from DH: repeat abortion rate 1 and 2 years after abortion .**

**Data Linkage with Lambeth Public Health data warehouse +/- National Abortion Data from DH: repeat abortion rate 1 and 2 years after abortion**

**Data Linkage with Lambeth Public Health data warehouse +/- National Abortion Data from Dept. of Health: repeat abortion rate 1 and 2 years after abortion.**

**Data Linkage with Lambeth Public Health data warehouse +/- National Abortion Data from Dept. of Health: repeat abortion rate 1 and 2 years after abortion .**

### 3 Selection and Withdrawal of Subjects

### 3.1 Inclusion Criteria

| Patients undergoing abortion under the NHS in Lambeth, Southwark and Lewisham who have consented for participation in the study. |
| --- |

### 3.2 Exclusion Criteria

| - Patients who do not speak English - Patients who will be leaving the country for 6 months after the abortion and hence will not be available for the follow up appointments or telephone follow-ups. - Patients who lack capacity to consent for themselves - Patients who attend for the pre-abortion consultation but do not go ahead with the abortion |
| --- |

### 3.3 Selection of Participants

| Patients undergoing induced abortion (any gestation, all ages) under the NHS in Lambeth, Southwark or Lewisham with one of the three abortion providers - King’s College Hospital NHS Foundation Trust, British Pregnancy Advisory Service and Marie Stopes International, who have consented to participate in the study. |
| --- |

### 3.4 Randomisation Procedure / Code Break

The design for this study will be that of a stratified block randomisation.

### Participants will be randomised by predetermined codes for each centre (strata) to intervention or control arm. The Randomisation list will be prepared by the Research statistician with a computer generated random number list stratified by centre and with random block sizes. The randomisation schedule will be incorporated into a dedicated electronic database and kept securely within this electronic system, inaccessible to the enrolment location. The allocation sequence will be concealed from the person enrolling and assessing participants to the study. The consent forms will be sent to the Chief Investigator based at King’s College Hospital at the end of each week. Participants will be assigned to the intervention or control arms based on the randomisation codes embedded within the dedicated electronic database system.

### 3.5 Withdrawal of Subjects

### Patients will be free to withdraw from the study anytime they wish. Baseline data collected on these subjects will be used for the analysis.

### 3.6 Expected Duration of Trial.

| Expected clinical participation of patients in the study will be for a period of 6 months. The total duration of the study will be 2-3 years to complete analysis of the secondary outcome of repeat abortions at 2 years. |
| --- |

**4. Study Procedures**

**4.1** Patient Information (Appendix 1):

Patient Information Sheet will be sent by Central TOP Booking Service when patients ring for their abortion appointment, after obtaining verbal consent for receiving information by post. Patients who decline postal contact will be given the information sheet when they attend for their abortion consultation.

**4.2**  Screening and eligibility:

Screening and Recruitment will be done by a member of the research team or a member of staff from the TOP Provider Unit when patients attend for their abortion consultation, after their abortion consultation.

**4.3** Baseline Assessment:

Patients approached for participation about the study will be requested to fill in a questionnaire (Appendix 2: Topic Guide A) to collect baseline socio-demographic and other relevant data relating to their sexual, reproductive and contraceptive history.

4.3(a) Retrospective data collection

Following minor amendment to the protocol (approved by NRES on 7th June 2013) we plan to collect retrospective data on abortions within the 2 years prior to recruitment in study participants. This data will allow us to better understand the contraceptive trajectories and potential future risk of repeat abortion in our recruited cohort. We will be obtaining this data through data linkage with the National abortion dataset held at the Department of Health.

**4.4** Informed Consent:

Written consent on a Consent form (Appendix 1) will be obtained from patients who are willing to participate in the study.

**4.5** Randomisation:

Patients will be randomised by predetermined codes for each centre (strata) to the intervention arm and control arm. The Randomisation list will be prepared by the Research statistician with a computer generated random number list stratified by centre and with random block sizes and held in a dedicated electronic database. The randomisation schedule will be inaccessible to the enrolment location. Patients will be allocated to the Intervention or Control arms based on the randomisation codes for each centre.

**4.6** Intervention:

1) Follow up consultation by telephone/face-face clinic appointment as per the patient’s preference with a Specialist from the Reproductive & Sexual Health Service at King’s College Hospital 2-4 weeks post-abortion. Women will be offered the opportunity to bring their male partners to the follow-up appointment if they wished, for participation in contraceptive counseling.

Further data will be collected during this follow-up consultation using a standardized questionnaire (Appendix 2 : Topic Guide B) to explore psycho-social, personal, partner-related and medical factors that could potentially influence contraceptive decision-making, compliance and continuation. The study participants will receive individualized contraceptive counseling & support and will be provided with a reliable contraceptive method of their choice if they are not already using one. Where issues such as alcohol/drug abuse, intimate partner violence, sexual exploitation, child protection, psychiatric disorders, significant psychological distress are identified, onward referral to appropriate agencies for investigation and support will be arranged. Where patients are not able to decide on a contraception plan, further follow-up appointments will be arranged as necessary to allow sufficient time for decision-making. If the patient prefers to see their GP/local contraceptive provider, a written referral will be made to the appropriate Health Care professional.

Patients will be given a telephone number and e-mail contact to contact the Chief Investigator/Research Nurse/Research Fellow if they need any additional support related to their contraception after their follow-up visit.

Management of patients who Do Not Attend (DNA) the follow-up appointment:

These patients will be contacted by telephone to identify the reason for the DNA (Appendix 2 : Topic guide C) and will be offered another suitable appointment for a telephone consultation or face-face clinic appointment with the Specialist according to the patient’s preference.

1. Telephone call 3 months post abortion to provide contraceptive support.

The Research Nurse/Fellow will contact the study participants in the intervention arm 3 months post-abortion by telephone and will carry out an interview with a standardized questionnaire (Appendix 2: Topic guide D) aimed at further data collection to include any changes in socio-demographic characteristics, personal, relationship, psychological, medical factors since the abortion and to capture information about any side-effects and compliance with the chosen contraceptive method. The Research Nurse/Fellow will also offer contraceptive support and refer back to the Specialist where necessary.

- 1. Study end points
- **Uptake and continuation of effective contraception at 6 months.**

Effective contraception will be defined as regular and consistent use of oral contraceptive pills/patches/vaginal ring (Nuvaring®)/ injectable contraception/ intrauterine contraception or the contraceptive implant. Use of barrier contraception or other methods such as withdrawal methods or natural family planning will not be considered as effective contraception due to their higher relative failure rate.

At 6 months post-abortion, the Research nurse/Fellow will contact patients in both intervention and control arms to assess contraceptive uptake and continuation. Data will be collected using a standardized questionnaire (Appendix 2: Topic Guide E) to explore factors that could have potentially influenced contraceptive decision-making, compliance and continuation. Information will also be obtained about the number of contacts patients in both groups have had with Health Care professionals relating to contraception since their abortion.

- **Repeat abortion at 1 and 2 years**

Anonymised data using unique patient identifiers such as Date of Birth and post code will be used to identify the proportion of study participants in each arm undergoing a repeat abortion within 1 year and 2 years following their abortion. This data will be obtained from the data routinely collected by the Public Health Department in Lambeth from the three abortion provider units for Lambeth, Southwark and Lewisham. It is possible that a small proportion of the study participants may have moved outside the boroughs of Lambeth, Southwark and Lewisham over a period of 2 years following their abortion and may have presented elsewhere for their repeat abortion. The Department of Health routinely collects statutory data returns from all abortion providers in England and Wales on all legal abortions. We will attempt to obtain permission from the Department of Health for Data linkage with the national abortion dataset for more complete information on repeat abortion rates in our study participants.

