### 2.2 Research Design

| This will be a randomized controlled study with an intervention arm and a control arm.  **Control arm:** Patients who have undergone an abortion under the NHS in Lambeth, Southwark and Lewisham (LSL) who will be recipients of current standard follow-up practice post-abortion, which is routine advice to see their G.P. or referring clinician 2 weeks post-abortion.  **Intervention arm**: Patients who have undergone an abortion under the NHS in LSL who will receive a specific follow up consultation with a Specialist from the Reproductive and Sexual Health Service at King’s College Hospital either by telephone or a face-face clinic appointment depending on patient preference at 2-4 weeks post-abortion to discuss contraception and a telephone follow up 3 months post abortion to provide further contraceptive support. Women will be offered the opportunity to bring their male partners to the follow-up appointment if they wished, for participation in contraceptive counseling.  Any other follow up interventions aimed at young people outside of our research intervention that may happen as a result of local commissioning recommendations in LSL will apply to participants in both the control and intervention arms. Hence any biases related to such interventions will be attenuated by the randomization design of the study.  Verbal consent to send an information leaflet about the research study will be taken by the Central Termination of Pregnancy (TOP) Booking Service when patients phone for their abortion appointment. Written patient information about the research study will be sent to potential participants along with the details of their TOP consultation appointment. Patients who do not want any documentation posted to their home address, will be approached at their pre-abortion consultation visit by a trained member of staff and offered a patient information sheet and invited to take part in the study.  Written consent for participation in the study will be obtained from patients when they attend for their TOP consultation appointment. Study participants will be randomized to the intervention or control arm by pre-determined randomization codes for each centre (strata). The Randomisation codes will be held by the Chief Investigator based in the Reproductive and Sexual Health Service at King’s College Hospital.  Patients randomized to the intervention arm will be contacted by phone by the Research nurse/fellow during the week after their TOP procedure and offered the choice of a telephone consultation or a face-face clinic appointment with a Specialist in the Reproductive and Sexual Health service at King’s College Hospital 2-4 weeks post-abortion to provide contraceptive support. For patients who choose to have a telephone consultation, a suitable time slot for the consultation will be agreed and will receive their Specialist consultation by telephone during this time. For patients who prefer a face-face consultation, a suitable appointment will be arranged to see the Specialist 2-4 weeks post-abortion. Patients in the intervention arm will also be informed about the telephone follow-up at 3 months and 6 months post-abortion for contraceptive support.  Patients randomized to the control arm will be contacted by phone by the Research nurse/fellow only at 6 months to assess contraceptive uptake and continuation.  **Primary outcome measures**  Uptake and continuation of effective contraception at 6 months. Effective contraception will be defined as regular and consistent use of oral contraceptive pills/patches/vaginal ring (Nuvaring®)/ injectable contraception/ intrauterine contraception or the contraceptive implant. Use of barrier contraception or other methods such as withdrawal methods or natural family planning will not be considered as effective contraception due to their higher relative failure rates.  **Secondary outcomes**  Repeat abortion at 1 and 2 years. |

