**5.2 Confidentiality:**

Patients will be given unique identifiers on entry to the study. To enable us to follow them up at 1 and 2 years to examine the repeat abortion rate without having to re-contact the patient, routinely collected data from the Public Health Department in Lambeth and the Department of Health will be matched to our research data using initials, date of birth and post codes. The link between the unique patient identifier and patient details will be maintained within a secure password protected NHS database, using all current guidelines employed by King’s College NHS Foundation Trust. Only NHS encrypted memory sticks will be used for data transfer. Once the database is locked at the end of the study period (3 years) all links will be destroyed by removing initials, dates of birth and postcodes from the study data.

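### Repeat abortion rests on data linkage alone, yet the linkage as worded does not call for the index abortion record, so a failed match looks the same as no repeat abortion

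*Protocol*

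**What the plan says.** - **Timing of recruitment.** Section 2.2: "Written consent for participation in the study will be obtained from patients when they attend for their TOP consultation appointment". Section 4.2 places recruitment "when patients attend for their abortion consultation, after their abortion consultation". Both come before the procedure.
- **Index abortion.** Section 3.2 excludes "Patients who attend for the pre-abortion consultation but do not go ahead with the abortion". Every eligible participant therefore has an index abortion, and Section 3.3 places it at one of three named providers.
- **Retrospective linkage.** Section 4.3(a): "we plan to collect retrospective data on abortions within the 2 years prior to recruitment in study participants". The source is the national dataset: "We will be obtaining this data through data linkage with the National abortion dataset held at the Department of Health".
- **Outcome linkage.** Section 4.7 uses linkage to "identify the proportion of study participants in each arm undergoing a repeat abortion within 1 year and 2 years following their abortion". The main source is "data routinely collected by the Public Health Department in Lambeth from the three abortion provider units". National linkage for the outcome is only to be attempted.
- **No other source.** Sections 5.2 and 11 say the outcome is obtained without contacting the woman again.
- **Keys.** Section 4.7 gives date of birth and postcode as examples. Sections 5.2 and 11 add initials.
- **After lock.** Section 5.2: "all links will be destroyed by removing initials, dates of birth and postcodes from the study data".
- **Index date.** It is not listed in any of the five topic guides in Appendix 2.

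**The concern.** When an outcome is ascertained only by linkage, absence of a record has two meanings: the event did not happen, or the woman was not found. A mistyped date of birth or a different postcode gives the second, and with all participants as the denominator it looks like the first. The usual safeguard is a record that every participant must have. Here it exists: the index abortion, at a provider that supplies the Lambeth data and, by Section 4.7, also makes statutory returns to the Department of Health. The plan does not ask for it.

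At stake is the reading of a named trial objective (Section 2.1). Under-counting would lower both arms' repeat-abortion rates and pull the absolute difference towards zero. A null result would then be harder to read as no effect. Once identifiers are removed, failed keys cannot be repaired.

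**Working it through.** **1. The windows as worded.** Retrospective window: from 2 years before recruitment up to recruitment. Outcome window: from the index abortion to 1 and 2 years after it. Recruitment is before the abortion, so the index record lies between the two.

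**2. The protocol's own sample size.** Section 6.1 gives 68% uptake, a 15-point difference, 95% power and two-sided 5%. For 68% v 83%, the pooled two-proportion formula gives 211 per arm, or 224 with continuity correction, against 223 stated. Then 446/0.60 = 743.3 and 743.3/0.65 = 1143.6, the stated 1144. The figure reproduces, but it concerns contraception at 6 months. The protocol gives no figure for repeat abortion after the index procedure or for linkage success.

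**3. Inputs for the illustration.** Per arm: 223/0.60 = 372. Assumed, not in the documents: true 2-year rates of 15% v 10% or 10% v 5%, and a linked fraction s between 0.7 and 1.0.

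**4. Equal linkage in both arms, unlinked women kept in the denominator without an event.** Observed rate = s × true rate, so the difference is multiplied by s and the risk ratio is unchanged.

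Power = Φ[(d − 1.96·SE0)/SE1], with SE0 from the pooled and SE1 from the separate variances. For 15% v 10% at s = 1: SE0 = 0.02425, SE1 = 0.02418, (0.05 − 0.04753)/0.02418 = 0.102, power 54%.

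| s | Observed difference, either case (points) | Power, 15% v 10% | Power, 10% v 5% |
|---|---|---|---|
| 1.0 | 5.0 | 54% | 74% |
| 0.9 | 4.5 | 49% | 69% |
| 0.8 | 4.0 | 44% | 63% |
| 0.7 | 3.5 | 39% | 57% |

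**5. Unequal linkage, no true effect.** At 15% in both arms with linkage of 85% v 75%: 0.15 × 0.85 = 12.75% and 0.15 × 0.75 = 11.25%, a false difference of 1.5 points (ratio 0.85/0.75 = 1.13).

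**6. What setting unlinked women to missing recovers.** If failure is unrelated to outcome, the linked women show the true rates on 372 × s per arm: 334.8, 297.6 and 260.4 for s = 0.9, 0.8 and 0.7. For 15% v 10% the difference returns to 5.0 points, but power is only 50%, 45% and 41%. Recoding repairs the estimates; lost power returns only if keys are corrected and women are found.

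**The case against.** The strongest reply is that Sections 4.3(a) and 4.7 name the events of interest and set no date limits for the extract. The index records already sit in the same routine data, and nothing bars retrieving them. This stands: a reader might infer that the index record is excluded, or that linkage success can never be known, and the protocol says neither. A reader might also infer a rule that unlinked women count as event-free. No such rule is written; it is only what follows from the all-participants denominator if nothing is done. An analysis plan could set a missing-data rule, but only if the data request shows who failed to match, and that request is described here.

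Bias between arms is also weaker than it first looks. Date of birth and postcode are on the baseline topic guide for both arms, and by Section 3.4 assignment follows receipt of the consent forms. No topic guide updates the postcode later, so the documents supply no mechanism for unequal failure. Step 5 shows a possibility, not an expectation.

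Three further replies have force. In the 15% v 10% case, power is only 54% with perfect linkage, so linkage would not be the main reason for an inconclusive result. An index match cannot detect women who later move, the loss that Section 4.7 itself acknowledges. And the procedure date must be known to staff to time the calls, so its absence from the topic guides does not show that it goes unrecorded.

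What remains is that no linkage check is planned, although a suitable record exists for every eligible woman.

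**Conclusion.** The point holds as a cheap improvement to ascertainment of a secondary outcome. As worded, the linkage does not call for the index record, and a failed match cannot be told from no repeat abortion. The main expected harm is under-counted rates, an absolute difference reduced in proportion to linkage, and some loss of power: at 90% linkage about half a point of a 5-point difference and about 5 points of power, at 70% about 1.5 points and 15 to 16 points of power (15% v 10% and 10% v 5% respectively). Equal failure leaves the risk ratio unchanged. A spurious effect is possible but less likely.

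These sizes rest on assumed repeat rates and linkage fractions, and on unlinked women being left in the denominator without an event. The primary outcome is unaffected.

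**What to change.** In Sections 4.3(a) and 4.7, request one extract from 2 years before recruitment to 2 years after the index abortion, including the index record. Then:

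1. Report the percentage of participants with a matched index record, by arm.
2. For women without a match, check and correct the keys before identifiers are removed at lock. Confirm with the provider that the abortion took place, since women who did not proceed are excluded.
3. Treat eligible women still unmatched as missing for repeat abortion, with unlinked taken as no event as a sensitivity analysis.
4. Use the index record date as time zero, or to confirm it, and count only later records as repeats. The time-to-event analysis in Section 6.3 needs this date.

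State one set of matching keys in Sections 4.7, 5.2 and 11.

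The cost is a wider date range in a request already being made, which the permission must cover, and one table. A few outcomes become missing. The index match gives only an upper bound on linkage sensitivity, because later moves and postcode changes remain untested; the report should say so.
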